The rTMS session will be scheduled with at least a one-week gap from the first plasticity assessment session to allow any potential carryover effects from the PAS to dissipate. This ensures that the subsequent rTMS treatment will not be influenced by the prior PAS intervention. The first participant was recruited on June 08, 2023. Fig 1 provides a schematic diagram illustrating the study design.

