**Fig 2 pone.0305013.g002:**
[figure not shown]
Schematic figure of plasticity assessment and intervention phases of the current study. (**A**). The plasticity assessment procedure consists of delivering 100 single TMS pulses over the left S1 using SI1 mV which will be applied before and after (0, 15, 30, and 60 min) PAS intervention. Throughout the PAS intervention, electrical stimulation of the right median nerve will precede TMS stimulation of the left S1 at an ISI of 20 ms. The plasticity will be then assessed using the ratio of the maximum CEA following PAS to the baseline CEA. CEA is quantified as the area under the curve of rectified TMS-EEG response within a time window of 25–275 ms from TMS stimulus onset. (**B**). Autistic participants will be further randomized to receive either a single session sham or active 20 Hz rTMS. The rTMS intervention will be delivered bilaterally over the S1 consisting of 120 trains of 50 pulses with an ITI of 30s (in total, 6000 pulses). The sequence of delivery will be randomized for each participant, that is left S1 followed by right S1 and vice versa, and the pulses will be applied at an intensity of 90% RMT. Following rTMS, on the same day, TMS-EEG plasticity assessment paradigm will be applied.

Participants will remain seated in a comfortable chair for the entire session, and to mask the auditory stimulation from TMS, white noise will be played through earplugs. The volume of the white noise will be carefully calibrated to effectively mask TMS-related sounds while staying within the participant’s comfort limits. The volume, will be gradually increased, monitoring the participant’s comfort level to find the maximum volume that is both comfortable and effective in masking the TMS clicks. Additionally, a layer of foam will be placed on the coil. This combination of foam and adapted white noise has been shown to achieve the greatest reduction in auditory evoked responses associated with the clicking sound of TMS [40].

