**Outcomes**
*Primary Outcome*. The primary outcome measure of this study is the PAS-induced LTP-like plasticity in the S1. PAS-induced LTP-like plasticity will be assessed using CEA. CEA is quantified as the area under the curve of rectified TMS-EEG response within a time window of 25–275 ms from TMS stimulus onset [44]. This chosen time window is designed to exclude any early artifacts and account for the subsiding effects of TMS. CEA will be averaged across 100 epochs from the electrodes of interest corresponding to the S1 region. The mean post-PAS CEA will be then divided by the pre-PAS CEA, reflecting the potentiation of CEA at each of post-PAS time points (0, 15, 30, and 60 minutes). Given that the timing of the post-PAS maximum potentiation could differ among participants, we will use the maximum CEA ratio for each participant for the statistical analysis [21].

To asses TR, the total score on the “touch” category of SPQ questionnaire will be used.

**A *Priori* power calculation** A sample size of *N* = 64 participants, consisting of 32 autistic participants and 32 neurotypical controls, has been determined as adequate for hypothesis testing. This sample size provides 90% power. This calculation is based on the preliminary data, the observed LTP-like plasticity difference of 20.6 points [15], as evidenced in our PAS-EEG pilot study involving both autistic adults and control subjects. Moreover, the same sample size is deemed suitable for evaluating hypotheses 2, offering an 80% statistical power to detect a moderate effect size (Cohen’s f2 = 0.15). These power calculations were executed using G*Power [45].

Drawing upon our previously published findings [15], we envision a "substantial" impact of active rTMS in a group of 16 autistic participants when compared to a sham group also consisting of 16 autistic participants. It is important to note that, given the relatively small sample size, the application of a single session, and the exploratory nature of this outcome, our approach to presenting results and their interpretation will extend beyond statistical significance values. Instead, we will place significant emphasis on estimated effects and their precision, including the calculation of 95% confidence intervals. This comprehensive set of information, combined with data related to tolerability, will play a pivotal role in shaping the design of future clinical trials.

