#### Statistical analysis

Hypothesis 1: To test this hypothesis, we will employ a linear regression model with CEA ratio (LTP-like plasticity) as dependent variable and study groups (autistic and neurotypical controls) as independent variable. Age, sex, hemisphere of PAS-EEG assessment, IQ and pre-PAS CEA (an index of individual baseline cortical excitability) will enter the model as ‘control’ independent variables. To ensure robustness, a model diagnostic will be conducted through visual inspection of model residuals for lack of normality, heteroscedasticity, linearity and outliers [46] and Cook’s distance [47] will be used to inspect for influential data points. Potential confounding effect of medication use among autistic adults on plasticity will be investigated in a post-hoc sensitivity analysis that will include mediation as an additional control.

Hypothesis 2: We will use a multivariate analysis of variance to test this hypothesis where TR, as dependent variable, is associated with plasticity in the autism group; S1 plasticity, study groups and their interaction will be the main predictors; and sex, age, hemisphere of PAS-EEG assessment and IQ will enter the model as controls. If the interaction between S1 plasticity and study group proves to be significant at confidence level 0.05, the model estimated slopes of S1 within each group will be investigate using graphs.

Hypotheses 3 & 4: In order to study the effect of active vs. sham rTMS on LTP-like plasticity, we will use an analysis of covariance with CEA ratio (LTP-like plasticity) as dependent variable, groups (active and sham rTMS) as fixed factor, and pre-rTMS CEA ratio as covariate. We will count discontinuation of rTMS session and adverse events to assess tolerability.

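### The H3 ratio has a denominator recorded after randomised rTMS, and the stated analysis cannot tell a waning or non-proportional shift in that baseline from a change in plasticity

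*Protocol article*

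**What the plan says.** The primary outcome is a ratio: "The mean post-PAS CEA will be then divided by the pre-PAS CEA" (Outcomes). Each participant contributes the largest of four such values: "we will use the maximum CEA ratio for each participant for the statistical analysis". All four share one denominator.

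The Fig 2 legend describes 100-pulse blocks "which will be applied before and after (0, 15, 30, and 60 min) PAS intervention". For the randomised phase it says: "Following rTMS, on the same day, TMS-EEG plasticity assessment paradigm will be applied". The article describes no TMS-EEG block before rTMS on that day, so the pre-PAS block of that session comes after rTMS.

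For Hypothesis 3 the Statistical analysis section states "we will use an analysis of covariance with CEA ratio (LTP-like plasticity) as dependent variable", with "groups (active and sham rTMS) as fixed factor, and pre-rTMS CEA ratio as covariate". The covariate is from the Phase I session: "The rTMS session will be scheduled with at least a one-week gap from the first plasticity assessment session" (Design and setting).

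The Hypothesis 1 model treats the denominator differently. There, "pre-PAS CEA (an index of individual baseline cortical excitability) will enter the model" as a control variable. The Hypothesis 3 paragraph does not mention pre-PAS CEA.

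**The concern.** Hypothesis 3 is about plasticity, meaning the response to PAS. The ratio measures that response cleanly if rTMS leaves CEA alone, or if it moves the pre-PAS and post-PAS blocks by the same factor. Otherwise part of any active-sham difference comes from the denominator.

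A direct effect is plausible on the article's own account. The Introduction describes the rTMS protocol as intended to strengthen inhibition. It cites lengthening of the cortical silent period, greatest at 6,000 pulses, which is the number used here. It also reports that the LTP reduction in the earlier motor-cortex trial was seen the day after rTMS, whereas here the assessment is on the same day. The one-week gap keeps PAS carryover out of the rTMS session, but the article describes no corresponding check on rTMS carryover into the PAS baseline.

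At stake is the mechanistic reading. The Hypothesis 3 estimates and intervals are meant to shape later trials, and a change in excitability described as reduced plasticity would misdirect them.

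**Working it through.** **No plan figure to reproduce.** The article gives no power, SD or effect size for Hypothesis 3, only 16 active and 16 sham participants.

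**Timing.** PAS is 180 stimuli at 0.1 Hz: 180 / 0.1 = 1,800 s = 30 min. If PAS follows the pre-PAS block directly, the 0-minute block starts about 30 min after that block ends and the 60-minute block about 30 + 60 = 90 min after. An rTMS after-effect therefore has between 30 and 90 minutes in which to wane between denominator and numerator.

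**Arithmetic on the ratio.** Let rTMS multiply pre-PAS CEA in the active arm by (1 + b), and let PAS truly raise CEA by g = 0.40 in both arms. Both values are assumptions. The sham ratio is 1.40. The active ratio is:

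- shift lasts and is proportional: (1 + b)(1 + g)/(1 + b) = 1 + g
- half gone by the post-PAS blocks: (1 + b/2)(1 + g)/(1 + b)
- all gone: (1 + g)/(1 + b)
- shift lasts, but PAS adds a fixed increment: (1 + b + g)/(1 + b)

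| b | Lasts, proportional | Half gone | All gone | Fixed increment |
|---|---|---|---|---|
| +20% | 1.40 | 1.28 | 1.17 | 1.33 |
| +10% | 1.40 | 1.34 | 1.27 | 1.36 |
| -10% | 1.40 | 1.48 | 1.56 | 1.44 |
| -20% | 1.40 | 1.58 | 1.75 | 1.50 |

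**The planned ANCOVA, simulated.** Inputs were 16 against 16, the maximum of four ratios, the Phase I ratio as covariate, two-sided alpha 0.05, 2,000 runs per case and no true effect on plasticity. Assumed: between-person log-SD of CEA 0.30, block-noise log-SD 0.10, SD of PAS gain 0.20. Entries are the mean active-sham difference in the ratio and the rejection rate.

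| b | Lasts, proportional | Half gone | All gone | Fixed increment |
|---|---|---|---|---|
| +20% | -0.002 (5%) | -0.127 (28%) | -0.252 (80%) | -0.068 (12%) |
| -20% | -0.002 (5%) | +0.185 (45%) | +0.371 (92%) | +0.097 (14%) |

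The first column is unbiased. In the others a rise in baseline pushes the estimate the way Hypothesis 3 predicts, and a fall pushes it the other way.

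**Two tempting repairs, same simulation, b = +20%.**

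- Adding post-rTMS pre-PAS CEA as a covariate leaves most of the bias: -0.228 (69% rejection) against -0.252 (80%) in the all-gone case.
- Regressing log maximum post-PAS CEA on Phase I values removes the bias if the shift has gone (-0.001, 6%). It creates bias if the shift lasts (+0.181 log units, 90%), where the planned ratio is sound.

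**What a baseline comparison can resolve.** For an unadjusted comparison, the 95% CI half-width is t(0.975, 30 df) × √(2/16) = 2.042 × 0.354 = 0.72 SD, and 80% power needs a difference of 1.02 SD. Adjustment for the Phase I value helps. Under the simulation's assumptions the variance of log pre-PAS CEA is 0.30² + 0.10² = 0.10 and the between-session correlation is 0.09/0.10 = 0.9. The residual SD is √(0.10 × (1 - 0.81)) = 0.138, and the half-width is about 2.045 × 0.138 × 0.354 = 0.10 log units, or about 10% either way. Those assumptions include no session-to-session drift, so the real interval is likely to be wider.

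**The case against.** The strongest reply is that the same-session denominator is the right choice. Normalising to the block just before PAS is what makes the ratio a measure of PAS-induced change. A denominator taken before rTMS would let a lasting direct effect into the ratio in full. This stands, and the first column of both tables bears it out.

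A reader might infer that any direct rTMS effect on excitability will be read as a change in plasticity, or that an active-sham difference can never be attributed to plasticity. The documents do not support that: bias needs waning or a PAS gain that is not proportional to baseline. The all-gone column is the extreme, since it requires the shift to have vanished by the 0-minute block. Nor do the documents show that the error favours Hypothesis 3. They say the rTMS strengthens inhibition, not whether CEA rises or falls. If CEA falls, the error runs against the hypothesis.

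A reader might also set these shifts against the 20.6-point difference in the power section. That figure is the autism-control difference for Hypothesis 1, and the article does not define its points, so it is no yardstick here.

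It can further be said that leaving pre-PAS CEA out of the Hypothesis 3 model is not itself an error. This also stands, because on the rTMS day that quantity is affected by treatment. Finally, Hypothesis 3 is labelled exploratory, and supporting comparisons may sit in a fuller plan not shown here. That lowers the weight of the point. It does not remove it: the model that the article fixes cannot separate the two explanations, and emphasis on estimates and intervals does not correct a bias.

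**Conclusion.** The point holds in a conditional form. It is firm that the denominator is recorded after randomised rTMS and that the stated ANCOVA, with arm and an earlier session's ratio, cannot separate a baseline shift from a changed response to PAS. Harm depends on two things that the documents do not settle: whether rTMS moves CEA at all, and whether that movement wanes before the post-PAS blocks or combines with PAS other than proportionally.

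The sizes are illustrative. With an assumed gain of 1.40 and a 20% rise, the spurious change in the ratio runs from nil to about -0.23 (1.17 against 1.40); with a 20% fall it runs from nil to +0.35 (1.75 against 1.40). The direction of bias for a given shift is firm; the sizes rest on assumed inputs. This is a worthwhile, inexpensive improvement to an exploratory analysis, not a flaw that invalidates it.

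**What to change.** Keep the planned ratio ANCOVA and pre-specify beside it:

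1. An ANCOVA of log post-rTMS pre-PAS CEA, active against sham, adjusted for log pre-PAS CEA from Phase I, reported as an estimate with a 95% CI.
2. Raw pre-PAS and post-PAS CEA by arm at each time point.
3. A rule for wording. If pre-PAS CEA differs between arms, or the CI in item 1 does not exclude a shift large enough to account for the ratio difference, describe the result as not separable from a change in excitability, rather than as reduced plasticity. One workable benchmark is the adjusted mean ratio in sham divided by that in active. This is the proportional rise in baseline that would produce the difference alone if it had gone by the post-PAS blocks (for example 1.40/1.17 = 1.20).

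Do not add post-rTMS pre-PAS CEA as a covariate, since treatment affects it. An ANCOVA of post-PAS CEA on Phase I values may serve as a sensitivity analysis only, because it is biased if the rTMS effect persists.

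The cost is one or two further exploratory analyses on data already collected, with no new procedures. Precision at 16 per arm is low, and a non-significant result in item 1 does not show that there was no shift.

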## Discussion

Our study will be the first to assess plasticity in the S1 in autistic adults using the innovative PAS-EEG. Completion of our study objectives will fill in a critical void in our understanding, i.e., if successful, we will identify the S1 hyper-plasticity as one brain mechanism underlying atypical TR and associated behavioral characteristics of autism. This information will provide us a biological target for testing ‘mechanism-driven’ interventions for tactile sensory difficulties in autism. Further, S1 hyper-plasticity may serve as a potential biomarker for TR and core behavioral characteristics in autism.

In conclusion, this protocol describes the study rationale, objectives, hypotheses, design and proposed methodologies of identifying the S1 plasticity in autistic adults. This study may provide a new line of translational inquiry that has not been explored in autism before.
